### Randomization and Blinding

We will use a computer-based stratified randomization approach to ensure an equitable allocation of participants across different treatment groups, stratifying based on 2 factors: the facility where the study participants are enrolled and the anatomical site of *M genitalium* infection (categorized as the urethra, rectum, or a combination of both). Participants will be randomly assigned to groups at a 1:1 ratio. Blinding will not be implemented, as treatment success will be determined using the NAAT, an objective test. After randomization, patients will receive their respective treatments and will be scheduled for a follow-up test of cure 3 weeks after completing the regimen, with a permissible range of 10-100 days. The test-of-cure content of the positive sites will be assessed using the NAAT. When treatment fails, the number of short tandem repeats in the protein MG309 will be analyzed to differentiate a new infection from a persistent one, as previously reported [26].

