### Statistical Analysis

The sample size has been determined based on previous treatment success rates and specific assumptions. In a preliminary study, we determined that sitafloxacin achieved a treatment success rate of 92.9% against *M genitalium* with the *parC* G248T (S83I) mutation, in conjunction with wild-type *gyrA* [20]. Furthermore, sitafloxacin demonstrated a 78.9% success rate against strains carrying the *parC* G248T (S83I) mutation based on our preliminary data, and Murray et al [27] reported a moxifloxacin success rate of 41.2% against such strains. Accordingly, the success rates of sitafloxacin and moxifloxacin were anticipated to be 80% and 42%, respectively. With a 5% significance level (2-sided) and 80% statistical power for precise analysis, we aimed to enroll 50 participants per group (totaling 100 cases), considering the prevalence of the G248T mutation. Additionally, an expected dropout rate of approximately 10% was factored in, leading to a calculated sample size of 112 participants, evenly distributed across treatment groups, to robustly assess the efficacy of sitafloxacin and moxifloxacin against specific mutations in *M genitalium*.

Primary analyses regarding efficacy primarily rely on the full analysis set (FAS), which encompasses all registered participants, excluding ineligible participants and those not receiving the study drugs. To evaluate sensitivity, the analysis will be conducted for the per-protocol set, which consists of the study population, excluding cases of major protocol violations and discontinuations from the FAS. To evaluate safety, the analysis will be conducted for the safety analysis set, which includes all registered participants except those not receiving the study drug. Baseline characteristics of the study participants, both discrete and continuous, will be summarized. Discrete data will be presented as frequencies and percentages, whereas continuous data will be presented as descriptive statistics such as the mean and SD. Data will be analyzed with STATA (version 16.0; StataCorp), SAS software (version 9.4; SAS Institute), and R (version 4.1.2; R Foundation for Statistical Computing); the sample size calculation was done using Power Analysis and Sample Size 2022 (NCSS Statistical Software).

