### Efficacy Outcome

The primary outcome is the treatment success rate, defined as the absence of the pathogen, as indicated through the NAAT. We set the superiority margin at 10%. The secondary outcomes include the change in bacterial load from pre- to posttreatment and the emergence of posttreatment nucleotide polymorphisms in mutant strains compared with those in pretreatment samples. The bacterial load will be measured as previously reported [28]. For the primary outcome in the FAS, with or without the G248T (S83I) mutation, rates and their 95% CIs will be computed. The chi-square test will be used to assess the statistical significance of treatment success between groups. This primary analysis will also be conducted for participants with the G248T mutation in the per-protocol set. In terms of secondary endpoints, differences, and rates of change in the bacterial load will be analyzed using either the 2-tailed Student *t* test or the Mann-Whitney *U* test. The rate and 95% CI of posttreatment resistance mutations in the FAS group will also be estimated using the positive cure confirmation results.

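### Randomisation is stratified by facility and infection site, but the stated primary test is a plain chi-square test that ignores both factors (minor; cheap to improve)

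*Protocol article*

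**What the plan says.** Under Randomization and Blinding, the protocol article describes "stratifying based on 2 factors: the facility where the study participants are enrolled and the anatomical site of" infection, with site "categorized as the urethra, rectum, or a combination of both". Allocation is equal: "Participants will be randomly assigned to groups at a 1:1 ratio".

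Under Efficacy Outcome, the primary result is reported as success rates in the full analysis set, "with or without the G248T (S83I) mutation, rates and their 95% CIs will be computed". The test is then named: "The chi-square test will be used to assess the statistical significance of treatment success between groups". It carries no strata, weights or covariates. The same section repeats the primary analysis in per-protocol participants with the G248T mutation. It also states "We set the superiority margin at 10"%.

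Under Statistical Analysis, the planning assumption is that "the success rates of sitafloxacin and moxifloxacin were anticipated to be 80% and 42%, respectively", with 50 per group before dropout.

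No section mentions a stratified test, a model adjusted for the randomisation factors, or a reason for leaving them out. An unqualified chi-square test between two groups is naturally read as one pooled 2×2 table.

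**The concern.** Stratified allocation balances the arms on facility and site, so differences in cure between strata contribute little to the true variability of the treatment comparison. A pooled test still counts those differences in its standard error. When the strata predict cure, that standard error is too large: the test rejects less often than its nominal 5% under the null, and a pooled CI for the difference is somewhat too wide. Analysing by the factors used in randomisation removes the mismatch.

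What is at stake is a little precision, and agreement between design and analysis. The validity of a positive result is not in question.

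**Working it through.** **The plan's own figures.** For 80% v 42%, p̄ = 0.61. The usual formula for two proportions gives

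n = [1.96·√(2·0.61·0.39) + 0.8416·√(0.8·0.2 + 0.42·0.58)]² / 0.38² = (1.352 + 0.535)² / 0.1444 ≈ 24.7, so 25 per group.

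With 50 per group, z = (0.38·√50 − 1.352)/0.635 = 2.10, a power of 98.2%. The dropout step reproduces: 100/0.9 = 111.1, or 112 when split evenly. The 50 per group does not follow uniquely from the stated inputs, but nothing below depends on how it was reached.

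**Number of strata.** Population and Eligibility Criteria can be read as listing two or three facilities. Three site categories then give 2×3 = 6 to 3×3 = 9 strata. On average that is 100/9 ≈ 11 to 100/6 ≈ 17 participants per stratum, and 50/9 ≈ 6 to 50/6 ≈ 8 in a subset of 50.

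**Mechanism.** Let B be the share of outcome variance that lies between strata. With good balance, the true variance of the difference is about (1 − B) times what the pooled test assumes, so its type I error is about 2Φ(−1.96/√(1 − B)). For B = 0.08 this is 2Φ(−2.043) = 4.1%. B cannot be negative, so ignoring the strata can only push the error below nominal.

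**Simulation.** Stratified blocks of 4 were simulated. The pooled chi-square test was compared with the CMH test,

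z = Σ(x_k − m_k·n_k/N_k) / √ΣV_k, with V_k = m_k(N_k − m_k)·n_k(N_k − n_k) / [N_k²(N_k − 1)],

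where, in stratum k, x_k is successes on sitafloxacin, m_k all successes, n_k participants on sitafloxacin and N_k all participants. The article gives no cure rates by stratum, so their effects are assumed and shown as a range. With 2 facilities × 3 sites, "moderate" means log-odds 0/−0.7/−1.0 by site and 0/−0.5 by facility; "strong" means 0/−1.2/−1.8 and 0/−0.8. The "spread" rows use 9 strata, with the stated logit range on each factor.

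Type I error, N = 100:

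| Strata | Chi-square | CMH |
|---|---|---|
| Moderate | 4.6% | 4.5% |
| Strong (two separate runs) | 4.3%; 4.1% | 5.2%; 5.1% |
| Spread 0 | 5.2% | 4.9% |
| Spread 1 | 4.6% | 5.0% |
| Spread 2 | 2.7% | 4.6% |
| Spread 3 | 1.3% | 4.7% |

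Spreads of 2 and 3 mean odds ratios of e² ≈ 7.4 and e³ ≈ 20 across each factor. They are extremes that show the shape of the effect, not expectations.

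Power at 80% v 42%, N = 100:

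| Strata | Chi-square | CMH |
|---|---|---|
| Not prognostic | 98.4% | 98.2% |
| Moderate | 98.2% | 98.2% |
| Strong | 98.5% | 98.9% |

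A visible gain at N = 100 needs a smaller effect than the plan assumes. With strong strata, power is 86% v 88% at 50% v 78%, and 80% v 83% at an odds ratio of about 3.7. The planned odds ratio is (0.80/0.20)/(0.42/0.58) = 5.5.

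Power at 80% v 42% in a subset of about 50 (G248T, prevalence assumed 50%):

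| Strata | Chi-square | CMH |
|---|---|---|
| Not prognostic | 80.7% | 77.8% |
| Moderate | 81.5% | 79.9% |
| Strong | 81.5% | 82.3% |

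A separate run with non-prognostic strata gave 83% v 80%. With 54 participants and spread 0 the figures were 83.8% v 81.9%; at spread 2 they were 86.4% v 90.5%. In a set this small, CMH loses up to about 3 points when the strata carry no information and gains only when they are strongly prognostic.

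**The case against.** The case for leaving the test alone is substantial.

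- **The error is on the safe side.** A reader might infer that ignoring the strata risks a false claim of superiority. It does not: the test becomes conservative, never liberal. This stands.
- **Strong strata are unsupported.** The Limitations section reports no discernible site difference for sitafloxacin. The reduced rectal efficacy it mentions concerns azithromycin, which is in neither arm. Nothing is said about site for moxifloxacin, or about facility. The Introduction presents resistance genotype as the driver of cure, and that is not a randomisation factor. This stands too, and it means that the 4% figure is conditional. It does not show that the strata are uninformative, since the control drug is not covered.
- **Power is not the issue.** A reader might infer that the chi-square test leaves the main comparison short of power, or that stratifying is free. Neither is supported: at the planned rates both tests reach about 98–99%, and in the G248T subset stratifying can cost power.
- **An analysis plan may add adjustment.** It is not shown, so one cannot say that the final analysis will ignore the strata. The article does, however, name the primary test, and a later stratified analysis would depart from the published one. The objection lowers the weight of the point without removing it.

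**Conclusion.** The mismatch is real and minor. Randomisation uses facility and site; the stated primary test uses neither. If the strata are strongly prognostic, the pooled test runs at about 4% instead of 5% with 100 participants; with moderate strata the two tests are practically the same. At 80% v 42% and N = 100, power is about 98–99% either way.

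These sizes rest on assumed stratum effects and stratum mixes, on blocks of 4, and, for the subset, on an assumed G248T prevalence of 50%. The direction (conservative) does not depend on the size of those effects. This is a cheap improvement, not a threat to the trial's conclusions.

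The 10% superiority margin, which an ordinary chi-square test of zero difference does not address, is a separate matter and adds no weight here.

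**What to change.** In the full analysis set, make the primary analysis a CMH test over facility and infection site, reported with a Mantel-Haenszel stratified risk difference and its 95% CI. Prespecify how sparse cells are pooled, for example by merging the both-sites category with another site category. Keep the unstratified chi-square test as a supporting analysis. The stratified CI can also be read against the stated 10% margin.

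For the G248T subset, either collapse the strata or keep the unstratified test, and say in advance which.

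The cost is a change of wording and a few lines of code, with no extra participants. In the full set with non-prognostic strata the loss is about 0.2 power points at the planned rates (98.4% v 98.2%). In a subset of about 50 it could reach about 3 points if the full stratification were carried over, which is why the subset needs its own rule.

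### Change in bacterial load is tested without baseline adjustment and with the test left open; a raw-scale difference would have little power and lean on baseline load

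*Protocol article*

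**What the plan says.** Under Methods, Efficacy Outcome, the article states: "The secondary outcomes include the change in bacterial load from pre- to posttreatment". The analysis is given later in the same section. Differences and "rates of change in the bacterial load will be analyzed using either the 2-tailed Student" t test or the Mann-Whitney U test. So two change measures are to be analysed, each by one of two unadjusted tests, and no rule is given for choosing the test.

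Measurement is by reference: "The bacterial load will be measured as previously reported [28". The article does not say whether differences are taken on the raw or the log scale, and it does not restrict the comparison to treatment failures.

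Two other statements bear on the point. Clearance is defined in the same section: "The primary outcome is the treatment success rate, defined as the absence of the pathogen, as indicated through the NAAT". Under Statistical Analysis, for strains with the G248T mutation, "the success rates of sitafloxacin and moxifloxacin were anticipated to be 80% and 42%, respectively", and "we aimed to enroll 50 participants per group (totaling 100 cases), considering the prevalence of the G248T mutation".

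**The concern.** A participant whose infection clears has a posttreatment load of zero or below detection. On the raw scale that participant's change is minus the baseline load, so it measures how heavy the infection was at entry and says nothing further about treatment. Copy numbers are usually strongly skewed, so a few heavy infections can dominate a mean. When most participants clear, an unadjusted comparison of raw differences can miss a real difference in clearance or pick up a chance difference in baseline.

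The open choice of test matters as well. The t test and Mann-Whitney can have very different power on the same data, and in an open-label trial a choice made after the data are seen is hard to defend.

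**Working it through.** **Plan's own figure.** The article gives no power or sample size for bacterial load. Its total of 112 reproduces from 100 evaluable participants and 10% dropout: 100 / 0.90 = 111.1, rounded up to 112 (56 per arm). That figure does not depend on this endpoint.

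**Step 1: the identity.** For a cleared infection on the raw scale, post minus pre = 0 - baseline = -baseline. Its rate of change is (0 - baseline) / baseline = -100%, whatever the baseline.

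**Step 2: how many participants it covers.** With 1:1 allocation and the planned rates, (0.80 + 0.42) / 2 = 0.61. Those rates are for G248T strains. For a full-analysis-set figure, assume that all *parC* mutants (68.3% in the Introduction) clear at these rates and that wild type clears at 100% on sitafloxacin and 96.5% on moxifloxacin:
- sitafloxacin: 0.683 × 0.80 + 0.317 × 1.00 = 0.863
- moxifloxacin: 0.683 × 0.42 + 0.317 × 0.965 = 0.593
- average: (0.863 + 0.593) / 2 = 0.728, about 73%

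**Step 3: power at 80% v 42% clearance.** Simulation with 50 per arm, two-sided 5%, 1,000 runs per row (Monte Carlo standard error at most √(0.5 × 0.5 / 1000) = 1.6 points). These inputs are assumptions, not in the article: log-normal baseline load, mean 4 log10; load in failures unchanged or 1 log10 lower, with SD 0.5 log10; cleared load 0, entered as 0 on the log10 scale. MW is Mann-Whitney. R² is the squared correlation of the raw difference with minus baseline. Power is in %.

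| Baseline SD (log10) | Load in failures | Raw diff, t | Raw diff, MW | R² | Log10 diff, t | Log10 diff, MW | Rate of change, t | Rate of change, MW | Chi-square on clearance |
|---|---|---|---|---|---|---|---|---|---|
| 0.5 | unchanged | 28 | 62 | 0.15 | 97 | 92 | 55 | 97 | 97 |
| 0.5 | 1 log10 lower | 6 | 7 | 0.98 | 96 | 91 | 56 | 97 | 98 |
| 1.0 | unchanged | 9 | 54 | 0.59 | 97 | 93 | 57 | 98 | 99 |
| 1.0 | 1 log10 lower | 2 | 5 | 1.00 | 94 | 92 | 59 | 98 | 99 |
| 1.5 | unchanged | 3 | 47 | 0.88 | 94 | 92 | 57 | 97 | 99 |
| 1.5 | 1 log10 lower | 1 | 6 | 1.00 | 87 | 89 | 58 | 98 | 99 |

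The raw difference is the weakest measure in every row. On the log10 scale, baseline explains only 3-24% of the variance of the difference. Rate of change by Mann-Whitney has nearly the power of the chi-square test on clearance, as expected when every cleared case is tied at -100%. On that same measure the t test has 55-59%, so the choice of test matters even there.

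**Step 4: error rate and sensitivity to baseline.** With 80% clearance in both arms, baseline SD 1, failures 1 log10 lower and no baseline gap, the raw tests reject in 3% (t) and 6% (Mann-Whitney) of runs. With a baseline gap of 0.5 log10 they reject in 18% and 66%. The unadjusted log10 difference rejects in 24% and 35%, and rate of change by Mann-Whitney in 5%. The gap is large: the standard error of the baseline difference is 1.0 × √(2/50) = 0.2, so 0.5 is 2.5 standard errors. It shows the direction of the sensitivity and is not a likely imbalance.

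**Step 5: gain from adjustment.** Take log10 posttreatment load with undetected samples at an assumed limit of 1 log10, baseline SD 1 and failures 1 log10 lower. ANCOVA on baseline has 93% power against 85% for the unadjusted log10 change at 80% v 42%, and 76% against 59% at 86% v 59%. The 85% lies below the 94% in the table because the assumed floor is higher. Over the settings at 80% v 42%, ANCOVA has about 90-97%, and a rank test on posttreatment load about 97%.

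**The case against.** The strongest reply is that the article never says the difference is raw. Measurement is by reference, and the scale, the rule for undetected samples and the criterion for choosing a test may stand in the full protocol or analysis plan, which are not shown. That stands. The absence of these details is not counted as an error here, and the raw-scale figures are conditional.

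A reader might also infer that the endpoint mostly compares baselines. The documents do not support that as a general statement. It fails on the log10 scale, and on the raw scale it depends on the load in failures: if that is unchanged, baseline explains between 15% and 88% of the variance.

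Nor is there systematic bias. Allocation is random and baseline load precedes treatment, so type I error stays at or below about 6%. Nor does the text offer four p values to pick from: both measures are to be analysed, and only the test is either/or.

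Finally, rate of change by Mann-Whitney is already in the plan, does not have the fault, and can beat ANCOVA. With 86% v 59% clearance, baseline SD 1, failures 0.5 log10 lower (SD 0.7) and a limit of 1 log10, it had 87% power against 79%. That also stands, and it is why a rank test may lead.

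What remains is what the article does state: unadjusted tests of change, one of whose natural readings is very weak, with the test left open.

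**Conclusion.** The point holds in a conditional and minor form. If differences are taken on the raw scale, about 61% of participants at the planned rates contribute only minus their baseline load. Power to show the planned effect is then about 1-28% by t test and 5-62% by Mann-Whitney. These ranges rest on 50 per arm, assumed log-normal baselines with SD 0.5-1.5 log10, and load in failures between unchanged and 1 log10 lower. The harm is lost power and sensitivity to chance imbalance, with type I error kept.

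On the log10 scale the problem is much smaller, though baseline adjustment still helps. The unnamed choice of test matters on either reading. The endpoint is secondary, and neither the primary chi-square analysis nor the sample size depends on it.

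**What to change.** Drop any raw-scale difference and the either/or choice, and name one analysis before the data are examined: log10 posttreatment load, with undetected samples set to the assay limit, compared by ANCOVA with baseline log10 load and the randomisation strata (facility and infection site) as covariates. Add a rank test on posttreatment load, or on rate of change, as the supporting analysis. Given the many values at the floor, the rank test could reasonably lead instead; state which.

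The cost is about one sentence, and baseline load is already measured because the endpoint requires it. The downside is that, with many values at the assay limit, the result will largely track clearance and add limited information beyond the primary endpoint.

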### Safety Outcomes

The side effects of each regimen will be reported during visit 2. Any unusual symptom or adverse reaction following the start of the regimens will be documented based on the division of the AIDS table for grading the severity of adult and pediatric adverse events (corrected version 2.1). Safety considerations include documenting adverse events, ranging from allergies and diarrhea to severe conditions such as aortic lesions, which are presented as frequency and group percentages for the safety analysis set.

### Data Collection and Management

A case report form (CRF) will be prepared by the appropriate and authorized individuals (investigators and physicians). All data recorded in the CRF must be consistent with the original material unless the data are recorded directly in the CRF as source material. Data will be collected at each visit (Table 1). All study findings and documents will remain strictly confidential, and patients will be identified only by their patient number or birth date, never by name, to protect their anonymity. The following data will be collected: date of birth (age), sex, nationality, race, medical history, history of current disease, complications, and allergies. Additionally, body weight and height will be measured at the first visit, along with vital signs at each visit, including the level of consciousness, body temperature (°C), blood pressure (mm Hg), pulse rate (beats per minute), respiratory rate, and physical condition at every visit, assessed through inspection, palpation, auscultation, and percussion.

**Table 1 table1:** Study calendar.

Study activities	Screening	Visit 1 (day 1)	Visit 2 (day 28 or 35)^a^
Informed consent	✓		
Confirmation of eligibility (inclusion and exclusion)	✓		
Enrollment	✓		
Clinical characteristics	✓		
Physical findings	✓	✓	✓
Treatment		✓	
Adverse events			✓
Test of cure			✓

^a^Permissible range of 10-100 days.

### Data Monitoring

No external data monitoring committee will be involved in this study. The first author will oversee the progression, completion of the intervention, and follow-up assessment of all participants.

### Ethical Considerations

This trial was granted ethical approval by the National Center for Global Health and Medicine of Japan’s certified review board (approval NCGM-C-004624-00) in October 2022, registered under jRCTs031230111. The study protocol and informed consent forms were approved by the local ethics committees at each study site before the commencement of the study. Adherence to human subject ethics review approvals was maintained in accordance with institutional guidelines. Informed consent was obtained from all study participants, with the process including clear communication about their right to opt out at any stage without penalty. The data collected during the trial were anonymized to ensure the privacy and confidentiality of participants. While no monetary compensation was provided, participants received the study drug and associated testing free of charge. This provision was documented and justified according to ethical standards and guidelines, ensuring voluntary participation and the integrity of the study.

